### Randomisation

A research nurse will attend the antenatal clinics at the respective study sites and screen pregnant women for eligibility. Eligible women will be approached and informed about the study. Those who agree to participate will be given more in-depth information about the study details and informed written consent will be obtained. A third party, who will not be involved in any part of the study, will develop a computer-generated randomised treatment allocation sequence for each study site using random block sizes of two to eight. The treatment assignments will each be placed in sequentially numbered, opaque, sealed envelopes. After obtaining informed written consent, the research nurse will select the next envelope in the sequence to determine the treatment allocation. A research assistant, who will not be involved in participant recruitment and will be blinded to the participants’ treatment allocation, will be responsible for the assessment of the study outcomes.

### Study interventions

This trial compares standard antenatal care to a brief one-to-one, 10-minute education session by a research nurse explaining the facts of influenza and influenza vaccine and answering participant questions. Briefly, usual antenatal care consists of routine checking of the maternal and foetal health by either clinic midwives or obstetricians along with health education to promote a healthy pregnancy. Special childbirth preparation and breastfeeding classes are available to the pregnant women for no additional cost. Routine antenatal care does not usually encompass specific education or recommendations about influenza vaccination. However, we will provide the standard care group participants with an educational pamphlet on influenza vaccine in pregnancy developed by the Hong Kong Centre for Health Protection (CHP), which is freely available in all antenatal clinics.

The brief education group will receive the usual care plus one-to-one, brief education that will focus on four key recommendations identified from the research literature [52,60,70-73]: (i) inform pregnant women of vaccination recommendations, (ii) encourage discussion with their HCPs, (iii) increase accessibility of vaccine (make referral to clinics where vaccine can be obtained), and (iv) provide credible information from the government official website and provide the website URL. Specifically, for participants in the education group in this study we will inform them about the: (i) WHO and Hong Kong CHP recommendations regarding influenza vaccine during pregnancy, (ii) potential complications associated with influenza infection during pregnancy and for young infants, (iii) safety of influenza vaccine for pregnant women and the foetus, and (iv) potential benefits of influenza vaccine for the pregnant women, the foetus and the infant, and (iv) where and how to get the influenza vaccine in Hong Kong.

To ensure the consistency of intervention, one research nurse will implement the intervention across the four sites. The research nurse has completed extensive education on the international and national vaccination guidelines and the benefits and safety of influenza vaccination for pregnant women, as well as the implementation of randomised controlled trials.

### Outcome measures

The primary study outcome is the influenza vaccination rate during pregnancy in the control and intervention groups. The secondary study outcomes are the proportion of participants initiating discussion about influenza vaccine with their health care provider, the proportion of participants seeking out influenza vaccine, and the influenza and influenza vaccine knowledge of participants in the control and intervention groups after receiving the intervention.

### Data collection and measurements

After recruitment, pregnant women who agree to participate in the study and have signed a written consent form will be asked to complete a standard baseline questionnaire that will include (i) key demographic data (i.e., age, marital status, education level, family income, and employment status); (ii) maternal health data (i.e., pre-existing health conditions, pregnancy related health problems, gravidity and parity, and expected date of confinement), and (iii) influenza and influenza vaccine knowledge. Participants will be followed up by telephone at two to three weeks after their expected confinement date by a study research assistant who will be blinded to their treatment group allocation. During the follow-up telephone interviews, information will be collected on (i) influenza vaccination data (i.e., vaccination status, reasons for receiving or not receiving the vaccine, discussion with HCPs, attempts to receive vaccine, anti-vaccination advice from HCP or family members, and vaccination status of family members); (ii) health status during pregnancy (i.e., perceived health status during pregnancy, pregnancy-induced medical conditions, and respiratory illnesses and symptoms); (iii) actual birth data (i.e., date of birth, gender, gestational age and birth weight); and (iv) postnatal influenza and influenza vaccine knowledge.

### Sample size

Previous Hong Kong studies show that the range of seasonal influenza vaccine uptake among pregnant women ranges from 1.7 to 5.0% [48,50,51]. From the literature, studies have shown that with provider-focused interventions, influenza vaccine uptake rates increased from 1 to 2% before the intervention to approximately 37% after the intervention [64-66,68]. In addition, the Meharry et al. study evaluating the educational pamphlet plus the verbal statement increased vaccine uptake from 46.9% in the control group to 86.1% in the intervention group [62]. Thus, an estimate of the ‘normal’ prevalence of influenza vaccine uptake among pregnant women in Hong Kong would be 5.0% and an increase to 20% would be highly conservative but still clinically meaningful. Thus, using a study power of .80 and a significance level of .05, then 76 participants would be required for each group calculated using the Gpower z-test [74]. After accounting for a loss to follow-up or dropout rate of around 20%, approximately 92 participants per group are required for a total of 184 participants. Recruitment would begin once the influenza vaccine is available, usually early October, and continue until all participants are recruited.

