**Methods:**

A randomised controlled trial will be conducted with pregnant women in at least the second trimester of pregnancy from four publicly funded hospital antenatal clinics in Hong Kong. Participants will be randomly assigned to either one of the two treatment groups: standard care (control) or standard care plus brief education (intervention). Pregnant women in the standard care group will receive the usual antenatal care with an educational pamphlet developed by the Hong Kong Centre for Health Protection and those in the intervention group will be provided with usual care plus a brief ten-minute education intervention. Content of the education session will cover four core components recommended in the research literature. The primary study outcome will be the proportion of participants who have received influenza vaccine during their pregnancy. A total of 184 pregnant women (92 per group) will be required to give an 80% power to detect a treatment effect of 15%.

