### Statistical analysis

The primary analyses will compare the proportion of participants in the two study groups who have actually received the influenza vaccine during their pregnancy. We will assess the equivalency of treatment group allocation by comparing the major socio-demographic indicators (age, education, income). Between-group comparisons will be made using a chi-squared test. The intention-to-treat principle will be used with missing values taken as no vaccination. Each estimate will be accompanied by a 95% confidence interval and a 5% level of significance will be used in all statistical tests. Other data analysis will include comparing the proportion of participants initiating discussion of influenza vaccine with their health-care provider and the proportion of participants seeking out influenza vaccination, again using chi-square tests. The knowledge level of the participants will be compared before and after the intervention using chi-squared test and student’s t-test. Data analysis will be performed using the Stata version 13.1 statistical software [75].

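### The 92 per group covers about 17% loss rather than the stated 20%, and the sizing does not carry through the rule that missing counts as not vaccinated; the cost is about 2 points of power on the sizing formula

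*Protocol article*

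**What the plan says.** The Sample size section takes control uptake of 5.0% ("vaccine uptake among pregnant women in Hong Kong would be 5.0" per cent) and an intervention rate of 20% ("an increase to 20% would be highly conservative but still clinically meaningful"). It sizes the trial "using a study power of .80 and a significance level of .05", with the G*Power z-test, and arrives at 76 women per group. It then allows for a "loss to follow-up or dropout rate of around 20%, approximately 92 participants per group are required for a total of 184 participants".

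The Methods paragraph of the Abstract carries the result forward: "A total of 184 pregnant women (92 per group) will be required to give an 80% power to detect a treatment effect of 15" per cent.

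The Statistical analysis section compares the two proportions by a chi-squared test and fixes how women without a known outcome are handled: "The intention-to-treat principle will be used with missing values taken as no vaccination".

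**The concern.** Two steps between the 76 and the 80% power claim do not follow from the plan's own inputs.

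- **Inflation for loss.** If a fraction d of women is lost, the evaluable number is N(1 − d), so the target is divided by 1 − d. The stated 92 is what results from multiplying by 1 + d.
- **Handling of missing outcomes.** Inflating for loss treats lost women as leaving the analysis, so that the remainder still show 5% versus 20%. The analysis section instead keeps every randomised woman in the denominator and counts the lost as unvaccinated. That restores the sample size but lowers both observed rates, and with them the difference under test. The sizing makes no allowance for this.

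At stake is whether 184 women give the stated 80% power for a 15-point effect under the analysis that the protocol prescribes.

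**Working it through.** **Inputs.** From Sample size: p1 = 0.05, p2 = 0.20, alpha 0.05, power 0.80, z-test for two proportions, 76 per group before loss, loss around 20%, 92 per group after loss. From Statistical analysis: chi-squared test, missing counted as not vaccinated. Sidedness is not stated. Two-sided is inferred because it reproduces 76, whereas one-sided gives 60.

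**1. Reproduce the 76.** With p̄ = (p1 + p2)/2, the pooled z-test without continuity correction gives

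n = [1.96 √(2p̄(1 − p̄)) + 0.8416 √(p1(1 − p1) + p2(1 − p2))]² / (p2 − p1)²

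For 5% versus 20%, p̄ = 0.125:

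n = [1.96 × 0.4677 + 0.8416 × 0.4555]² / 0.15² = (0.9167 + 0.3834)² / 0.0225 = 75.1, rounded up to 76. The plan's figure is confirmed and its method identified.

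**2. The inflation step.**

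- Division: 76/0.80 = 95 per group (190 in total).
- Multiplication: 76 × 1.2 = 91.2, rounded up to 92 (184 in total), as stated.
- Loss that 92 covers: 1 − 76/92 = 17.4%.
- Evaluable women at 20% loss: 92 × 0.80 = 73.6 per group.

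**3. Power among completers at 20% loss.** Power = Φ{[(p2 − p1)√n − 1.96 √(2p̄(1 − p̄))] / √(p1(1 − p1) + p2(1 − p2))}. For 5% versus 20%:

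| Evaluable per group | Z-test power |
|---|---|
| 73 | 78.8% |
| 73.6 | 79.2% |
| 74 | 79.4% |
| 76 | 80.5% |

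**4. Power under the stated missing-data rule.** Assume 20% loss in both arms, unrelated to vaccination, and take 5% and 20% as rates among women with known status. The analysed rates are 0.05 × 0.80 = 4% and 0.20 × 0.80 = 16%, a 12-point difference. All randomised women are in the denominator.

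At 92 per group, p̄ = 0.10: [0.12 × √92 − 1.96 × 0.4243] / 0.4157 = (1.1510 − 0.8315)/0.4157 = 0.768, and Φ(0.768) = 77.9%.

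Required for 80%: (0.8315 + 0.3499)² / 0.12² = 96.9, so 97 per group (194 in total). At 95 per group the power is 79.2%.

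**5. Sensitivity to the loss rate,** same rule, 92 per group:

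| Loss | Z-test power |
|---|---|
| 5% | 85.4% |
| 10% | 83.1% |
| 15% | 80.6% |
| 17.4% | 79.4% |
| 20% | 77.9% |

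**6. Exact power of the chi-squared test.** Enumerating all pairs of binomial outcomes at two-sided 5%:

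| Per group and rates | Uncorrected | Continuity-corrected |
|---|---|---|
| 73, 5% v 20% | 81.6% | 74.5% |
| 74, 5% v 20% | 82.2% | 75.2% |
| 92, 4% v 16% | 81.1% | 71.5% |

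**The case against.** A reader might infer that the trial is underpowered, or that its 80% claim fails outright. The documents do not support that.

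- **The planned test is chi-squared; the z-test is only the sizing formula.** The uncorrected test has exact power of about 81% at 92 per group for 4% versus 16%, and above 81% in the completers-only case. This stands, and it limits the point to the stated derivation. The continuity-corrected figure of 71.5% is no ground for a stronger claim, because the protocol names no correction.
- **Both figures are hedged as approximate, and the operation is never stated.** This stands in part. Multiplication by 1.2 is inferred from the arithmetic, and 92 would also be a correct division at about 17% loss. But at 17.4% loss the missing-data rule still gives 79.4% by the z-test, and the rule is still absent from the sizing.
- **The 5% control rate is the top of the cited range.** Holding the effect at 15 points with 20% loss and the same rule, z-test power at 92 per group is 81.2% for a control rate of 3.9% and 88.3% for 1.7%. So the planning rates are rougher than the error at issue. This bears on its importance, not on whether the stated figure follows from the stated inputs.
- **5% and 20% might already count missing women as unvaccinated.** Z-test power at 92 would then be 87.4%. The text does not exclude this reading, but no inflation for loss would then be needed, and the plan inflates.

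Nor does the sizing contradict the analysis rule. Inflating for loss and then counting the lost as unvaccinated is an incomplete allowance, not two incompatible instructions.

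**Conclusion.** The stated 92 per group does not follow from 76 evaluable women and 20% loss, and the 80% power claim leaves out the effect of the missing-data rule on the rates compared. Both are errors in stated figures, and both are minor. The inflation step alone costs 3 women per group and under 1 point of power. With the missing-data rule, the gap is 5 women per group (92 against 97) and about 2 points on the sizing formula.

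This rests on a two-sided test, loss of 20% in both arms and unrelated to vaccination, and 5% and 20% being rates among women with known status. With loss of 15% or less, the z-test figure stays above 80%. The point calls for a correction to the text and does not question the design.

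**What to change.** Keep 92 per group. In the Sample size section, state that 92 covers about 17% loss. Add that at 20% loss, with missing counted as not vaccinated, it gives about 78% power by the z-test (about 81% by exact calculation for the uncorrected chi-squared test) for 4% versus 16%, and list the assumptions about loss. Amend the power sentence in the Abstract to match. This costs wording only.

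If a larger target is preferred, 95 per group (6 more women in total) corrects only the inflation arithmetic and still gives 79.2% by the z-test under the planned analysis. A claim of 80% on that basis needs 97 per group (194 − 184 = 10 more women in total).

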### Statistical analysis

The primary analyses will compare the proportion of participants in the two study groups who have actually received the influenza vaccine during their pregnancy. We will assess the equivalency of treatment group allocation by comparing the major socio-demographic indicators (age, education, income). Between-group comparisons will be made using a chi-squared test. The intention-to-treat principle will be used with missing values taken as no vaccination. Each estimate will be accompanied by a 95% confidence interval and a 5% level of significance will be used in all statistical tests. Other data analysis will include comparing the proportion of participants initiating discussion of influenza vaccine with their health-care provider and the proportion of participants seeking out influenza vaccination, again using chi-square tests. The knowledge level of the participants will be compared before and after the intervention using chi-squared test and student’s t-test. Data analysis will be performed using the Stata version 13.1 statistical software [75].

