## Methods

This study will be an open-label, randomised controlled trial. Pregnant women in at least the second trimester of pregnancy will be recruited from the antenatal clinics of four public hospitals geographically dispersed throughout Hong Kong. Ethical approval has been obtained from the Institutional Review Boards of all the participating study sites and informed written consent will be obtained from participants who have agreed to participate but prior to randomisation. The design, implementation and reporting of this study will conform to the guidelines listed in the ICH-GCP, Declaration of Helsinki, standard CONSORT 2010 Statement [69].

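### Randomisation is stratified by the four sites, but the chi-squared tests for the primary outcome and the two secondary proportions ignore site: valid, slightly conservative, and free to improve

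*Protocol article*

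**What the plan says.** Under Randomisation, the protocol article describes a "computer-generated randomised treatment allocation sequence for each study site using random block sizes of two to eight". Under Methods, the sites are the "antenatal clinics of four public hospitals geographically dispersed throughout Hong Kong". Allocation is therefore stratified by site, with four strata, and site is the only stratification factor named.

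Under Statistical analysis, the primary comparison is of the proportions vaccinated in the two groups, and "Between-group comparisons will be made using a chi-squared test". The secondary proportions are discussion with a provider and "the proportion of participants seeking out influenza vaccination, again using chi-square tests". Knowledge is treated differently: "The knowledge level of the participants will be compared before and after the intervention using chi-squared test and student’s t-test". The section mentions no site term, stratified test or adjusted model. Each estimate is to carry a 95% confidence interval, and missing outcomes count as not vaccinated.

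Under Sample size, the trial is sized with an unstratified two-proportion z-test, "using a study power of .80 and a significance level of .05", for 5% against 20%.

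**The concern.** Blocking within site makes the arms nearly equal in size at each hospital, so differences in uptake between hospitals largely cancel out of the treatment difference. A plain chi-squared test takes its variance from the pooled uptake, which still contains those differences. If uptake varies by site, the standard error is too large for the design, and the p-value and interval err on the cautious side.

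Uptake could plausibly vary by site. The Background says that public antenatal clinics do not give the vaccine and that women must find it in scattered private settings, and the four hospitals are spread across the city. What is at stake is some precision and power in a trial sized for 80% power. The validity of a positive result is not in question.

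**Working it through.** **Inputs from the protocol article.** Four sites with separate blocked sequences (Randomisation); 92 per group, 5% against 20%, power 0.80, alpha 0.05, loss of about 20% (Sample size); missing counted as unvaccinated (Statistical analysis).

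**Assumptions.** Equal sites of 23 per arm (92 / 4); 20% loss in both arms, so each true rate is multiplied by 0.8; the site-level control rates shown in the table; a common odds ratio of (0.20/0.80) / (0.05/0.95) = 4.75.

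**Step 1: the plan's own figure.** Two-sided z-test with pooled variance and no continuity correction:

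n = [1.960 × √(2 × 0.125 × 0.875) + 0.842 × √(0.05 × 0.95 + 0.20 × 0.80)]² / 0.15² = (0.917 + 0.383)² / 0.0225 ≈ 75.1, rounded up to 76.

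The stated 76 per group is reproduced, so the sizing also takes no account of site.

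**Step 2: why the crude test is conservative.** For equal sites with pooled observed rates p_s and mean p̄:

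mean of p_s(1 − p_s) = p̄(1 − p̄) − Var(p_s).

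The crude test uses p̄(1 − p̄); the stratified test uses the left side.

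- *Control 1, 2, 5 and 12%.* The odds ratio of 4.75 gives 4.6, 8.8, 20.0 and 39.3% under intervention. Averaging the arms and multiplying by 0.8 gives p_s = 0.022, 0.043, 0.100 and 0.205, so p̄ = 0.0927, p̄(1 − p̄) = 0.0841 and Var(p_s) = 0.0050. The within-site share is 1 − 0.0050/0.0841 = 0.94. The crude standard error is too large by 1/√0.94, about 3%.
- *Three sites at 1.7%, one at 14.9%.* The intervention rates are 7.6% and 45.4%, so p_s = 0.037 (three times) and 0.241, p̄ = 0.0882, p̄(1 − p̄) = 0.0804 and Var(p_s) = 0.0078. The share is 0.90, and the standard error is too large by about 5%.
- *Identical sites.* Var(p_s) = 0, so nothing is lost.

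**Step 3: simulation.** Pearson chi-squared (crude) against Cochran-Mantel-Haenszel (CMH), both without continuity correction, with 200,000 to 400,000 trials per pattern. Monte Carlo standard errors are about 0.1 point for power and 0.05 for type I error. Separate runs agreed to about 0.3 points on power and 0.1 on type I error.

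| Control rates by site (assumed) | Power, crude | Power, CMH | Type I, crude | Type I, CMH |
|---|---|---|---|---|
| 5% at all four | 81.2% | 81.2% | 4.2% | 4.4% |
| 2, 4, 6, 8% | 79.2% | 79.4% | 4.3% | 4.5% |
| 1.7, 3.9, 4.9, 5.0% | 70.5% | 70.8% | 4.4% | 4.5% |
| 1, 2, 5, 12% | 73.3% | 74.7% | 4.0% | 4.7% |
| 1.7, 1.7, 1.7, 14.9% | 67.2% | 70.4% | 3.7% | 5.0% |

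The table should be read across, not down. Power falls between rows mainly because a fixed odds ratio gives a smaller average risk difference when the rates are uneven, or when their mean is lower as in the third row. Only the gap within a row is due to the choice of test.

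**Step 4: what part of the type I shortfall is due to site.** With identical sites the crude test is already at 4.2%, because events are few and the statistic is discrete. Ignoring site takes off a further 4.2 − 4.0 = 0.2 points in the fourth pattern and 4.2 − 3.7 = 0.5 in the fifth.

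**The case against.** The case against acting is substantial. The crude test is valid, does not inflate type I error, and matches the z-test used for sizing. The loss depends wholly on assumed site rates. The Hong Kong figures cited in the article run only from 1.7% to 5.0%, and with sites inside that range the gain from stratifying is about 0.3 points. Scattered private provision describes access in general and does not show that uptake differs by recruiting hospital. A statistical analysis plan that is not shown may already specify a stratified analysis. All of this stands, and it is why the severity is low. It does not remove the point: the article names its test, and that test leaves out the only factor on which randomisation was stratified.

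A reader might infer more than the documents support:

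- *That every comparison is a plain chi-squared test.* It is not; knowledge also uses a t-test.
- *That false positives are at risk.* The error runs the other way.
- *That the whole gap between about 4% and 5% comes from ignoring site.* Most of it is discreteness (step 4).
- *That the power loss is large.* A loss of about 6 points (87.0% against 93.0% at 76 per arm, no loss to follow-up) appears only with control rates of 0.5, 0.5, 1 and 18%, which nothing in the documents suggests.

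**Conclusion.** The point holds as a mismatch of low severity between design and analysis. For the primary outcome and the two secondary proportions, the stated test ignores the stratification by site. It stays valid and becomes slightly conservative if uptake differs by site.

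Under the assumed patterns the power forgone is about 0 points with identical sites, 0.2 to 0.3 with mild spread, 1.4 with control rates of 1, 2, 5 and 12%, and about 3 with one outlying site. These figures assume four equal sites, a common odds ratio of 4.75 and 20% loss counted as unvaccinated; true site-level uptake is unknown. Stratifying costs essentially nothing: no loss in the table, and 0.2 points at most in a further run with identical sites and 76 per arm (83.0% against 83.2%). No conclusion of the trial is endangered by leaving the test as it is.

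**What to change.** In the Statistical analysis section, make the primary test a Cochran-Mantel-Haenszel test stratified by site, reported with a Mantel-Haenszel risk difference or risk ratio and its 95% confidence interval. Use the same for discussion with a provider and for vaccine-seeking. Keep the unstratified chi-squared test as a sensitivity check. If a statistical analysis plan already stratifies by site, align the article with it.

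The change should be fixed before outcomes are seen, so that there is no later choice between crude and stratified results. It costs about one sentence, is standard in the named software, and needs no new data or participants. The planned 184 women (92 per group) do not change.

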### Study participants

Pregnant women attending the antenatal clinics of the four public hospitals will be screened for eligibility. Eligible patients are pregnant women: (a) with a singleton pregnancy; (b) at least 18 years of age; (c) in at least the second trimester of pregnancy; (d) Cantonese speaking; (e) Hong Kong resident; (f) without serious medical or obstetrical complications; (g) have not received the influenza vaccine in this pregnancy; and (h) who will be staying in Hong Kong for at least two weeks after birth.

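### Counting every missing outcome as not vaccinated, with a 95% interval computed as if it were observed, can bias the effect estimate and its interval in a direction that depends on who is lost

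*Protocol article*

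**What the plan says.** All references are to the protocol article.

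- Statistical analysis, on missing outcomes: "The intention-to-treat principle will be used with missing values taken as no vaccination". The same section adds: "Each estimate will be accompanied by a 95% confidence interval". The between-group test is chi-squared at the 5% level.
- Sample size, on the planning rates: "influenza vaccine uptake among pregnant women in Hong Kong would be 5.0% and an increase to 20% would be highly conservative". On the numbers: "using a study power of .80 and a significance level of .05, then 76 participants would be required for each group", and "After accounting for a loss to follow-up or dropout rate of around 20%, approximately 92 participants per group are required".
- Data collection and measurements: vaccination status is collected when women are "followed up by telephone at two to three weeks after their expected confinement date", by an assistant blinded to allocation.
- Study participants, criterion (h), admits women "who will be staying in Hong Kong for at least two weeks after birth".

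The article describes no second analysis of the primary outcome with missing values handled differently.

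**The concern.** A woman who cannot be reached after delivery has unknown status. The public antenatal clinics do not give the vaccine (Background), and the article describes no source for status other than the call. The rule gives her a definite negative answer and leaves her in the denominator. This has two consequences.

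- Each arm's rate falls by its own loss fraction, unless the lost women were in fact unvaccinated. The fall in points is larger in the arm with higher uptake.
- The interval uses all 92 women per arm as if every answer had been given, so it carries no uncertainty about the unknown ones.

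The trial is open-label, and only one arm has the ten-minute session with the nurse, so equal response in the two arms cannot be taken for granted. At stake is the reported size of the effect and the range around it, which readers will use to decide whether brief education is worth adopting.

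**Working it through.** **Inputs.** Planned uptake 5% v 20%, power 0.80, alpha 0.05, 76 per group before and 92 after allowance for about 20% loss (Sample size). Missing = not vaccinated and a 95% interval (Statistical analysis). Two assumptions are mine: the estimate is the absolute difference in rates, because the abstract states the treatment effect as 15%; and, except where stated, loss within an arm is unrelated to vaccination.

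**Plan's own figure.** Two-sided pooled z-test, mean rate 0.125:

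n = [1.96 × √(2 × 0.125 × 0.875) + 0.8416 × √(0.05 × 0.95 + 0.20 × 0.80)]² / 0.15² = (0.9167 + 0.3834)² / 0.0225 = 75.1, rounded up to 76. This matches the plan. Then 76 × 1.20 = 91.2, rounded up to 92.

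**Equal 20% loss, planned rule.** Each rate is multiplied by 0.80.

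- Control 0.05 × 0.80 = 4%; intervention 0.20 × 0.80 = 16%; difference 12 points.
- Half-width = 1.96 × √[(0.04 × 0.96 + 0.16 × 0.84) / 92] = 8.5 points. Interval 3.5 to 20.5, width 17.0.

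**Equal 20% loss, women with known status.** 92 × 0.80 = 73.6 per arm.

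- Difference 15 points.
- Half-width = 1.96 × √[(0.05 × 0.95 + 0.20 × 0.80) / 73.6] = 10.4 points. Interval 4.6 to 25.4, width 20.8.

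The planned interval is about 18% narrower (17.0 / 20.8 = 0.82).

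**Coverage of the true 15 points** (400,000 simulated trials, Wald intervals):

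- Planned rule: 87.0%; 12.7% of intervals lie wholly below the true value and 0.3% wholly above.
- Known status: 94.5%.
- Planned rule at 10% loss: estimate 13.5 points, coverage 92.6%.

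**Unequal loss under the planned rule.** Expected difference = 0.20 × (1 − intervention loss) − 0.05 × (1 − control loss). The splits are illustrative; the article gives none.

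| Loss, control / intervention | Expected difference | Coverage |
|---|---|---|
| 10% / 30% | 0.140 − 0.045 = 9.5 points | 71% |
| 30% / 10% | 0.180 − 0.035 = 14.5 points | 94% |
| 40% / 0% | 0.200 − 0.030 = 17.0 points | 93% |

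The error in the difference is 0.05 × control loss − 0.20 × intervention loss. It is negative unless control loss is at least four times intervention loss. At exactly four times, the two errors cancel by accident.

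**The test.** Power under equal 20% loss is 77.9% with the planned rule and 79.2% with known status by formula (81.1% and 81.7% simulated). With 5% uptake in both arms and equal 20% loss, the planned rule rejects in 4.3% of trials.

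**The opposite assumption.** If all the lost women were unvaccinated, the planned rule is unbiased at 15 points. Known-status women would then show 0.05 / 0.80 = 6.25% v 0.20 / 0.80 = 25%, a difference of 18.75 points.

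**The case against.** - **The rule is a familiar, cautious choice.** At low uptake, no is the right answer for most lost women: if loss is unrelated to vaccination, about 95% of those lost from control and 80% of those lost from intervention. The article's wording on loss also covers dropout, not only failed calls. This stands as a reason to keep the rule. It does not make the interval right, because the remaining 20% in the intervention arm is what moves 20% to 16%.
- **The test is hardly touched.** Under equal loss this is correct, and the point is confined to estimation.
- **A ratio would escape under equal loss.** 20/5 and 16/4 are both 4. This stands, but the plan expresses its effect as an absolute 15%, and the ratio also moves under unequal loss (14/4.5 = 3.1 at 10%/30%; 20/3 = 6.7 at 40%/0%).
- **Known-status analysis has its own bias.** The 18.75 points above overstate by 3.75, more than the 3 points by which the planned rule understates in the equal-loss case. So it is a companion, not an unbiased replacement.
- **Differential loss is speculative.** Both arms meet the nurse at consent, controls receive a pamphlet and the caller is blinded. No figure in the article supports any particular split.
- **The full plan may add sensitivity analyses.** It may, and their absence from an article is not the complaint. The point rests on the rule that the article states.

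A reader might infer that the rule will produce false-positive trials. The plan's own rates do not support that: with 5% uptake in both arms and 30%/10% loss, the false difference is 0.05 × 0.20 = 1 point and rejection is about 5.5%.

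**Conclusion.** The stated rule can give a biased effect estimate and an interval that is too narrow and off-centre. At the plan's rates, with 20% loss equal and unrelated to vaccination, the estimate is 12 instead of 15 points and coverage is about 87% instead of 95%. Under unequal loss the error can go in either direction, from 9.5 to 17 points in the illustrative splits. Each arm's rate is unbiased only if the lost women were truly unvaccinated. The conclusion rests on the planning rates, the expected 20% loss, and the absolute difference as the effect measure.

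Two stronger readings are not supported. One is that the rule always shrinks the effect, or is always conservative; the direction depends on who is lost and from which arm, which the article cannot tell us. The other is that criterion (h) adds avoidable loss because the required stay can end before the call. The call is by telephone, the stay is a minimum, and no figure shows that any woman would be missed. What remains is that Study participants counts from the birth while Data collection and measurements counts from the expected date. Those two windows should be reconciled.

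**What to change.** In Statistical analysis, keep missing = not vaccinated and add beside it:

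- the risk difference and 95% interval from women with known status, or from a simple within-arm multiple imputation. The imputation model must stay small, because only about 4 control events are expected (73.6 × 0.05 = 3.7);
- a statement that the effect size will be described from both analyses;
- the number lost in each arm;
- what each analysis assumes: the planned rule, that the lost women were unvaccinated; the known-status analysis, that loss is unrelated to vaccination within arm. State also that the latter would give 18.75 instead of 15 points if every lost woman were unvaccinated.

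The chi-squared test need not change. Separately, reconcile the dates from which criterion (h) and the follow-up call are counted.

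Cost: a few sentences and no new data. The added interval is about 4 points wider (20.8 v 17.0, or 23%), and the report must explain two estimates instead of one.
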